***Omentectomy decreases insulin resistance:***

Epidemiologic *(Cefalu 1995, Shimokata 1989, Ferrannini 1997, Fujimoto 1999, Lamarche 1998, Carey 1996, O'Shaughnessy 1995)* studies (including our own) have correlated visceral fat with insulin insensitivity in both animals and humans. Several possible mechanisms have proposed this association. These include increased delivery of FFAs *(Bujalska 1997)* to the liver *(Bjorntorp 1990, Williamson 1996)* and/or abnormal expression of various cytokines (IL-6, TNF-α) and adipokines such as resistin, adiponectin, leptin and others *(Hotamisligil 1996, Steppan 2001).* Barzilai et al. *(1999)* demonstrated that surgical removal of visceral fat rapidly improved hepatic and peripheral insulin action in young rats and in rats predisposed to obesity and diabetes *(Gabriely 2002)*. Interestingly, removal of an equivalent amount of fat from the subcutaneous tissue in the same rats did not alter hepatic nor peripheral insulin sensitivities. Our recent studies in the conscious dog model (preliminary data) demonstrated that the removal of visceral fat resulted in improvement of insulin action in the absence of caloric restriction, challenging the notion that nutrient excess per se is the prominent cause of insulin resistance in obesity.

Thörne et al. *(2002)* randomized 50 non-diabetic morbidly obese subjects (BMI>35 kg/m2) to either adjustable gastric banding (AGB) alone or AGB plus partial removal of the greater omentum (omentectomy). The improvements in oral glucose tolerance, insulin sensitivity and fasting plasma glucose and insulin were 2-3 times greater in omentectomized subjects as compared to control subjects (P<0.05) and these were associated with a near 15% excess weight loss (p=0.07) over a two year period. There were no associated adverse effects related to omentectomy. It is important to note that the use of the adjustable gastric banding results in significantly less effective weight loss and less effective improvement in carbohydrate metabolism than RYGB and VSG. Ceelen and coworkers *(2003)* followed 625 subjects after laparoscopic AGB for three years and noted the median excess weight loss was limited to 47%. This is in comparison to a median excess weight loss up to 70% following RYGB.

1. **Rationale and Specific Aims**

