**Study Plan**

We propose a randomized study to evaluate changes in glucose, amino acid, and fatty acid metabolism at early and late stages after bariatric surgery. We will explore the mechanism(s) of changes in any of these substrates by examining alterations in the secretion and action of energy regulating peptides and of the inflammatory responses. Morbidly obese subjects will be divided into two groups with 150 participants in each arm; 75 Caucasian participants and 75 African American and Hispanics:

**Group I**: will undergo bariatric surgery (RYGB, VSG, AGB)

**Group II:** will undergo bariatric surgery (RYGB< VSG< AGB) combined with omentectomyThe study will include Caucasians, African Americans and Hispanics matched for BMI, gender and age. It will include short and long term aims with respect to the time after the surgical intervention in addition to the pre-operation basal period.

We will also obtain fat and muscle samples from normal weight individuals undergoing other abdominal surgery to serve as controls.

**Specific Aim 1: Determine the mechanism for the metabolic improvements after** bariatric surgery

Metabolic effects of the surgery will be examined at 4-weeks postoperatively, at a time when early improvements in insulin sensitivity are observed in the majority of Caucasian subjects and when changes in BMI or body composition are minimal. Subjects will also be studied at 6, 12 and 24 months when weight loss becomes significant. Subjects may also be asked to return at 3, 4, and 5 years post-operatively in order to continue to observe changes that occur in the long-term. We will evaluate which improvements following RYGB can be related to early alterations in specific energy-regulatory peptides and/or inflammatory factors and which simply follow the decrease in body weight.

**Specific Aim 2: Explore the mechanism for the blunted and delayed metabolic improvement after** bariatric surgery **in African Americans and Hispanics**

Comparison of the temporal changes in the metabolic profile will be made under matched experimental conditions for Caucasians, African Americans and Hispanics. Gene microarray analysis from two adipose tissue depots as well as skeletal muscle will be used to obtain an unbiased approach that will guide data interpretation.

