***Enrollment for morbidly obese patients*:**

- Patients approved for RYGB, VSG, or AGB are reported to study coordinator
- Coordinator or study nurse screen subjects via Star Panel to determine eligibility

Subjects determined to be good candidates for the study are contacted and the study is described to them. If they show interest, detailed information, including the consent form, is sent to them to read over. The coordinator follows up to respond to questions or concerns.

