**Day of Surgery:**

- Subject is met in pre-op area and told about study. Subject is asked if he/she would be willing to let surgeon take muscle and fat samples during the operation. If subject agrees, he/she is consented and surgeon is notified.

**Randomization:** The randomization schedule will be generated by statistical software. The randomization code will be generated using a permuted block size of four. No other restrictions will be used. As each subject is recruited, the randomization is assigned by the coordinator and the surgeon is notified. The PI, [name], will not be involved in the selection and allocation of patients. All recruited patients and researchers involved in the evaluation of the end-points will be blinded to the treatment assigned throughout the whole study period. No interim analyses will be carried out during the course of this study.

1. **Study Procedures**

**Provide a description of what the participants will experience. For example, a description of the instructions that will be given to the participants, activities in which they will engage, the length and timing of involvement, and the circumstances under which they will provide data (e.g., phone calls, spending time in an uncomfortable position, group assessments, one-on-one interview, videotaping, audiotaping, etc.)**

***Subjects who participate in metabolic chamber (the subjects will be assigned to the metabolic chamber in the preoperative period and will have chamber studies again at 6-, 12-, and 24-months post-operatively, as well as 3, 4, and/or 5 years post-operatively, unless otherwise noted):***

**Study Day 0:** Subject reports to the GCRC in the afternoon. The following are performed:

- Measurements of Height, Weight, and Body Circumferences.
- History and Physical Examination
- Performance of EKG (if over age 40)
- Performance of serum pregnancy test (if fertile female)
- Answer SF-36 Questionnaire
- Orders will be written for no food and caffeine after 20:00. They will be made completely NPO after 24:00

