Initial analyses will examine the short-term effects of race and surgical procedure (bariatric surgery + omentectomy), and the interaction effect of race by surgical procedure on change in measures of body composition, inflammatory factors, hormones, energy-related peptides, and health-related quality of life following bariatric surgery. The general case statistical method is mixed-model repeated measures analysis of variance with tests of: (a) the within-subjects effect of time; (b) the between-subjects main effects race and surgical procedure; and (c) race by procedure by time interaction effects. Simple contrasts will be used to test effects at postoperative week four in relation to preoperative measure. Statistical tests of main and interaction effects of race and omentectomy on any contrast are analogous to interaction of these effects with the within-subject change scores (simple contrasts). Assuming a within-subject correlation between longitudinal data points that is as low as 0.35 in the combined sample (n=132), power is adequate (85%) to detect a small effect (d=0.3) of time for any contrast. Power to detect, for any contrast, medium (f=0.30) overall main effects of race and omentectomy and the race by omentectomy interaction effect is 92%. This statistical design will also be applied within each racial group (n=66) to more explicitly examine the effect of omentectomy, and within each surgical group (n=66) to more explicitly examine the effect of race. For these analyses, the power to detect medium to large (d=0.70) effects for any contrast is 80%.

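### Both arms mix three bariatric operations that the protocol says differ in effect, yet no stated model names the operation, so an unequal mix between racial groups would distort the race comparisons of Aims 2 and 3

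*Protocol*

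**What the plan says.** **Population.** Under Study Plan, Group I "will undergo bariatric surgery (RYGB, VSG, AGB", and Group II lists the same three operations combined with omentectomy. The enrolment section agrees: "Patients approved for RYGB, VSG, or AGB are reported to study coordinator".

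**Aim 1.** Its heading refers to bariatric surgery in general, but its analysis sentence reads "We will evaluate which improvements following RYGB can be related to early alterations in specific energy-regulatory peptides and/or inflammatory factors".

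**Differences between operations.** The Background subsection on omentectomy states that "adjustable gastric banding results in significantly less effective weight loss and less effective improvement in carbohydrate metabolism than RYGB and VSG". It cites a median excess weight loss of 47% in a banding cohort followed for three years, against a median of up to 70% after RYGB.

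**Models (Section 10).**
- The short-term model tests time, "the between-subjects main effects race and surgical procedure", and their interactions. In both the short-term and long-term text, surgical procedure is glossed as bariatric surgery plus omentectomy, so the factor means omentectomy or not.
- The long-term mixed model adds clinical covariates without naming them. Its examples of time-sensitive covariates are weight loss and syndrome X symptoms.
- The month-24 completer analysis returns to the short-term method.
- Aim 3 reuses these methods to compare African American and Hispanic patients with omentectomy against Caucasian patients without it.

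**Allocation and matching.** Randomisation uses a "permuted block size of four. No other restrictions will be used". The racial groups are to be "matched for BMI, gender and age"; type of operation is not among the matching variables.

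**The concern.** By the protocol's own account, type of operation is prognostic for weight and carbohydrate metabolism. It is chosen clinically rather than assigned by the trial, and no stated model names it.

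The consequence differs by contrast:

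- **Race (Aim 2) and the Aim 3 comparison.** Neither is protected by randomisation. If one racial group has more banding than the other, the difference between operations enters the race effect. Aim 3 is the more delicate case, because the protocol hopes to find its two groups comparable. A difference in operation mix could create that comparability as easily as destroy it.
- **Omentectomy.** It is randomised, so the mix is balanced in expectation. Variation between operations goes into the error term and costs some precision.
- **Time (Aim 1).** A pooled change over time describes the enrolled mix. It does not answer a question worded for RYGB alone.

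**Working it through.** **1. The plan's own long-term figure.** Section 10 gives 80% power for d = 0.81 with 25 per group, two-sided alpha 0.05. A two-group noncentral t (48 df, noncentrality 0.81 × √(25/2) = 2.86) gives 80.1%, so the figure reproduces. The calculation uses one common SD, with no separate allowance for type of operation.

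**2. Shift in a race contrast when the mix differs.**

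Shift = (difference in banding share between racial groups) × (difference in outcome between operations).

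- Difference between operations, from the Background: 70 − 47 = 23 points of excess weight loss. This is an upper figure: it compares medians across studies, and the RYGB value is an upper limit.
- Difference in share: not in the protocol, so a range is assumed. For simplicity VSG is treated like RYGB, as the Background suggests similar weight loss.

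| Difference in banding share (assumed) | Shift, at most | In SD units, if SD = 20 | In SD units, if SD = 15 |
|---|---|---|---|
| 10 points | 0.10 × 23 = 2.3 | 0.12 | 0.15 |
| 20 points | 0.20 × 23 = 4.6 | 0.23 | 0.31 |
| 30 points | 0.30 × 23 = 6.9 | 0.35 | 0.46 |

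The SDs of 15 and 20 points are also assumptions. For scale, the long-term Aim 3 comparison is sized for d = 0.81. If the mix is the same in both groups, the shift is zero.

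**3. Precision of the long-term omentectomy contrast.** With banding share p and gap G, leaving out the operation multiplies the error variance by 1 + p(1 − p)G²/SD². If d = 0.81 were scaled to the SD within one operation, it would shrink by the square root of that factor:

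| p | G | SD | Variance factor | Power, 25 per group |
|---|---|---|---|---|
| 0.05 | 12 | 20 | 1.02 | 79% |
| 0.05 | 23 | 20 | 1.06 | 78% |
| 0.10 | 23 | 20 | 1.12 | 76% |
| 0.20 | 23 | 20 | 1.21 | 72% |
| 0.30 | 23 | 15 | 1.49 | 63% |

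Example, third row: 0.10 × 0.90 × 23² = 47.6; 1 + 47.6/400 = 1.12; 0.81/√1.12 = 0.77; power 76%. Every row depends on assumed p and SD and on that scaling of d. The 12-point gap is roughly half the maximum.

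**4. Week four.** No calculation is offered. The protocol gives no difference between operations at that time, and Aim 1 says body composition has hardly changed by then.

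**The case against.** **Covariates belong in the SAP, and the long-term model has room for them.** This stands in part. The unnamed clinical covariates could include the operation, so it would be too strong to say that no model could hold it. But the short-term and completer models list their terms and have no such place. The protocol also names a determinant of outcome in its Background and then defines surgical procedure so as to leave it out.

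**The power loss is speculative.** Largely correct. A reader might carry the 23-point gap into the week-four contrast (d = 0.70, 33 per group) and conclude that its power is well below 80%. The documents do not support that. The gap comes from long-term weight loss, and banding was followed for three years. The protocol also never says that d is scaled to an SD within one operation; if d refers to the SD of the mixed population, the stated powers already include this variation.

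**The race bias is conditional.** Correct. Nothing in the protocol shows that the operation mix differs by race, and Aim 2 promises matched experimental conditions. That promise is not carried into the listed matching variables or the models, so the possibility stays open. Stratifying the omentectomy randomisation by operation would not close it, since race is not allocated.

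**The RYGB wording in Aim 1 is residue.** Probably so. Aim 1's heading, the central hypothesis, the arms and the enrolment section all use the wider term or list three operations. A reader might infer that Aim 1 was meant for RYGB patients only; the text as a whole does not support that. The sentence still needs correcting.

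**Conclusion.** The concern holds in a limited form. The trial pools three operations that the protocol says differ on weight and carbohydrate metabolism, and the short-term and completer models leave the operation out. The exposed results are the non-randomised ones: the race effects serving Aim 2 and the Aim 3 comparison. For long-term excess weight loss the possible distortion is at most about 2.3 points per 10-point difference in banding share. This takes the protocol's cross-study gap at face value and treats VSG like RYGB.

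It should not be read as showing that the race effects are biased, which would need an operation mix that differs by race. Nor is the omentectomy effect biased: randomisation protects it in expectation, and it loses only precision, by an amount the document cannot fix and which is small if banding is rare. The change is worth making because it is nearly free and protects the comparisons that randomisation cannot.

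**What to change.** In Section 10, under Specific Aims 1 and 3:

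- Add the planned bariatric operation (RYGB, VSG or AGB, as approved before enrolment) and its interaction with time as fixed effects in the short-term, long-term and completer models, including the Aim 3 comparison. Using the approved operation keeps it a baseline variable.
- Use a distinct name for the omentectomy factor, so that surgical procedure is not mistaken for type of operation.
- Tabulate operation by racial group and study arm. If an operation occurs almost only in one racial group, the model cannot separate the two, and the report should say so.

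Under Specific Aim 1, reconcile the RYGB sentence with the arms: either refer to bariatric surgery, or state that RYGB-specific conclusions come from the RYGB patients.

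The cost is wording and a few degrees of freedom, provided that the approved operation is captured as a data field. The change needs no extra patients or visits and no change to treatment.

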**Specific Aim 3: Explore whether combining omentectomy with bariatric surgery helps accelerate and sustain post-surgical metabolic improvements especially in the more refractory African American and Hispanic populations**

Removal of the greater omentum will be combined with bariatric surgery randomly in a subgroup of subjects. We hypothesize that onset time and magnitude of the metabolic improvements (as in **Specific Aim 1**) in African Americans and Hispanics who undergo bariatric surgery combined with omentectomy will be comparable to Caucasians undergoing bariatric surgery alone (without omentectomy). As already indicated, the African American cohort of patients manifested significantly improved insulin sensitivity to glucose metabolism. We seek to test the mechanisms of improvement and to uphold the null hypothesis that the two said groups are comparable over time. In all three aims, the studies proposed include determination of the following parameters:

1. Regional fat stores and muscle distribution by body circumference measurements and DEXA scans
2. Adipocyte size, tissue macrophage content and macrophage gene expression
3. Diurnal and food-induced secretion of adipokines such as leptin, resistin and adiponectin
4. Diurnal and food-induced secretion of the energy regulating-peptides such as ghrelin and PYY
5. Kinetics of blood glucose, amino acids and fatty acids
6. Insulin responsiveness and secretion
7. Levels of inflammatory markers such as CRP, IL-6, TNF-α2R (measure of TNF-α in plasma)
8. **Animal Studies and Previous Human Studies**

**Describe the process and outcome of the animal and/or laboratory studies that have been done. Also, if any previous human studies have been done (e.g., Phase I, other phases maybe in a different population or for a different indication).**

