***Statistical Methods, Sample Size, and Power Estimates:*** We based sample size estimates on historical case volumes (>600 procedures per year), patient demographic distributions (70% Caucasian, 25% African American, 5% Hispanic, 80% female 20% male). Persons who consent to participate will be enrolled in both the short and long term phases of the study. We assumed attrition for the short-term phase, which entails data points through postoperative week four, to be negligible, and for the long-term study, which entails a two-year postoperative follow-up period, to be ~ 25% by postoperative month 24. We based this rate on reported attrition following bariatric surgery over a comparable time, and the rate is assumed to be comparable between experimental groups. Anticipated effect sizes were based on previous research or standard conventions for large, medium, and small effects *(Cohen 1988)*. Unless noted, power estimates were determined using standard methods and software (Power and Precision™ v. 2.0, nQuery Advisor™ v. 3.0) for non-directional tests at the 0.05 alpha level.

Demographic information such as age, race, and gender will be tabulated. Descriptive statistics, including means, standard deviations, and ranges for continuous measures, as well as percentages and frequencies for categorical measures will be presented. Statistical analyses will be performed using standard packages (SPSS or SAS).

**Specific Aim 1:** The short-term phase of the investigation will include a group of 66 Caucasians and group of 66 African Americans and Hispanics (each of the two groups randomized to 33 bariatric surgery and 33 bariatric surgery + omentectomy). The long-term phase of the investigation will include at least 100 patients (25 in each of the four racial and procedure groups).

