**Specific Aim 3:** Analyses addressing **Specific Aim 3** will be performed using the statistical methods described above for both the short and long term phases of the investigation (mixed-model repeated measures analysis of variance and mixed effects modeling). Two subject groups will be included in these analyses: (a) African American and Hispanic patients receiving bariatric surgery plus omentectomy, and (b) Caucasian patients receiving bariatric surgery without omentectomy. Our hypothesized mechanism for the effects of omentectomy and race implies that these two groups will experience comparable outcomes over time. Given our previous data, which demonstrated a large effect of race (d > 1.5) on weight reduction following bariatric surgery, and our hypothesis that omentectomy will blunt the disparity in African Americans and Hispanics, effect sizes were set at > 0.81. The power to detect an effect of group (d=0.81) on a within-subject contrast (change over time) in the short-term phase of the study (33 patients per group) is 90%. Power is 80% to detect a comparable effect (d=0.81) on any contrast in the long-term study (minimum group size = 25). In order to analyze the effect of omentectomy independent of race, a sample size of 11 participants per group would allow us to detect a 25% difference in insulin sensitivity between groups, with an *alpha* value of 0.05 and power of 80% (*beta* = 0.2). This is based on data on glucose kinetics obtained previously in obese participants (Klein 2004). A difference of this magnitude is clinically meaningful because it represents the lower end of the observed effect of current treatment strategies for insulin resistance, such as moderate weight loss (Kelley, 1993; Kirk 2009; Tiikkainen 2004; Ross 2000) and thiazolidinedione therapy (Schrauwen-Hinderling 2008; Li 2007; Coletta 2009) which increase hepatic and skeletal muscle insulin sensitivity by 25-50%.

1. **Privacy/Confidentiality Issues**

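### Aim 3 aims to uphold a null hypothesis of comparability, but plans only difference tests and states power for refuting that hypothesis, with no equivalence margin

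*Protocol*

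**What the plan says.** Protocol, Rationale and Specific Aims, Specific Aim 3: the onset and size of metabolic improvement in African American and Hispanic patients given omentectomy "will be comparable to Caucasians undergoing bariatric surgery alone (without omentectomy". The goal follows: "We seek to test the mechanisms of improvement and to uphold the null hypothesis that the two said groups are comparable over time".

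Protocol, Statistical Considerations, Specific Aim 3: the expectation is repeated ("Our hypothesized mechanism for the effects of omentectomy and race implies that these two groups will experience comparable outcomes over time"). The analyses "will be performed using the statistical methods described above for both the short and long term phases of the investigation", that is, by the repeated-measures analysis of variance and mixed-effects models set out for Aim 1. Power is given for a difference: "The power to detect an effect of group (d=0.81) on a within-subject contrast (change over time") is put at 90% with 33 per group in the short term, and 80% with at least 25 per group in the long term. The general power paragraph says that, unless noted, estimates are "for non-directional tests at the 0.05 alpha level".

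The protocol states no equivalence or non-inferiority margin, confidence-interval criterion or equivalence test.

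The Aim 1 paragraphs of the same section do plan the race-by-omentectomy interaction, the effect of omentectomy within each racial group, and the effect of race within each surgical group. The Aim 3 paragraph restricts its comparability analysis to the two named cells and does not make the conclusion depend on those other analyses.

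**The concern.** A difference test can reject equality, but failing to reject does not establish it. When the hypothesis of interest is the null, a smaller or noisier sample makes the hoped-for result more likely. The long-term comparison has fewer patients per group, so non-significance is easier to obtain there.

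The stated power does not help. It says how often the trial would contradict Aim 3 if a 0.81 SD gap remained. It does not say how often the trial could validly show comparability if the groups were truly alike.

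There is also a question of attribution. The two cells differ in both race and omentectomy, and omentectomy is randomised within race, not between these cells. Similar outcomes could therefore arise because omentectomy helped or because the racial gap was small in this sample. The protocol has analyses that can separate these explanations, but the Aim 3 conclusion is not tied to them.

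At stake is whether the Aim 3 result can be interpreted. A residual gap of moderate size could be reported as comparability, with the stated power cited in support.

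**Working it through.** **Inputs.** Two-sided alpha 0.05; d = 0.81 with SD taken as 1; 33 per group short term and 25 long term (all from Statistical Considerations). The 25 agrees with the stated attrition of about 25%: 33 × 0.75 = 24.75. The protocol gives no margin, so a range is assumed below.

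**Step 1: reproduce the stated power.** Two-sample t-test, df = 2n − 2, noncentrality d√(n/2).
- n = 33: 0.81 × √16.5 = 3.29, critical t = 1.998, power 90.0% (stated 90%).
- n = 25: 0.81 × √12.5 = 2.86, critical t = 2.011, power 80.1% (stated 80%).

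A one-sided test would give 94.6% and 88.1%, which does not match. The stated figures are correct as power of a two-sided difference test.

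**Step 2: chance of a non-significant result when a real gap remains** (1 − power).

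| True gap (SD) | 33 per group | 25 per group |
|---|---|---|
| 0.3 | 78% | 82% |
| 0.4 | 64% | 72% |
| 0.5 | 48% | 59% |
| 0.7 | 20% | 32% |
| 0.81 | 10% | 20% |

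**Step 3: precision.** The 95% CI half-width is t(0.975) × √(2/n).
- n = 33: 1.998 × 0.246 = 0.49 SD.
- n = 25: 2.011 × 0.283 = 0.57 SD.

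A result that just misses significance has an estimate about equal to the half-width. Its upper limit is then about twice that: 1.0 SD or 1.1 SD.

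**Step 4: power for the claim Aim 3 wants to make.** Two one-sided 5% tests, which is the same as requiring the 90% CI to lie inside ± margin. True difference 0, by simulation.

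| Assumed margin (SD) | 33 per group | 25 per group |
|---|---|---|
| 0.81 | 89% | 76% |
| 0.75 | 83% | 67% |
| 0.6 | 56% | 35% |
| 0.5 | 29% | 10% |
| 0.4 | 3% | 0.4% |

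By the normal approximation, n per group for 80% equivalence power is 2 × ((1.645 + 1.282)/margin)². This gives 27 at 0.81 SD, 48 at 0.6 SD and 69 at 0.5 SD.

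**Step 5: sensitivity to the other sample size.** The Study Plan gives 150 per arm, split into 75 Caucasian and 75 African American and Hispanic patients, so 75 per cell rather than 33. At 75 per cell a 0.5 SD gap is non-significant 14% of the time. Equivalence power is above 99% at 0.75 SD, 84% at 0.5 SD and 57% at 0.4 SD. The size of the problem therefore depends on which sample size is meant. The mismatch between goal and test does not.

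**The case against.** The strongest reply has four parts.

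*The protocol never states that p > 0.05 proves comparability.* This is true. A reader might infer that a non-significant difference will be declared proof that omentectomy closes the racial gap, but the text does not go that far. It speaks of comparable outcomes, of diminishing racial differences and of blunting a disparity, and the aim is headed as exploratory. What stands is narrower: the stated goal is to "uphold the null hypothesis that the two said groups are comparable over time", and the only analysis given for that comparison is a difference test.

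*The attribution problem is already handled.* A reader might also infer that the trial cannot separate an omentectomy effect from a small racial gap. The documents do not support that: the interaction, the randomised omentectomy contrast within each racial group and the race contrast within each surgical group are all planned for both phases. The Aim 3 paragraph also sizes an omentectomy analysis independent of race. What remains is that the Aim 3 conclusion is not made conditional on any of them.

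*Little is lost at the protocol's own effect size.* At a margin of 0.81 SD, equivalence power is 89% and 76%, close to the stated 90% and 80%. This is fair, but 0.81 SD is what the protocol itself calls a large effect, and it was never proposed as a margin. It was set against a previous racial effect above 1.5 SD on weight reduction, whereas Aim 3 covers many metabolic, hormonal and inflammatory outcomes. For the same reason, half of that weight-loss effect (0.75 SD) is only an illustration here.

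*Dropout is already allowed for.* The 25 per group includes the expected attrition, and the mixed models keep partial data. This is accepted. The point is only that a smaller sample makes non-significance more likely.

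A separate analysis plan might add a margin. It would still have to displace the goal and the power justification that the protocol fixes.

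**Conclusion.** The concern holds in a limited form. The Aim 3 goal and its planned test point in opposite directions, and the stated power, though arithmetically right, does not bear on the hypothesis. With 33 or 25 per group, a true 0.5 SD gap would be non-significant 48% or 59% of the time, and the 95% CI half-width would be 0.49 or 0.57 SD. Under an equivalence criterion the planned groups support only a wide margin, near 0.81 SD.

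These figures assume a two-group t-test on a standardised change score, equal groups, and (for equivalence power) a true difference of zero. They use the cell sizes that the Aim 3 paragraph uses. At the Study Plan's 75 per cell they would be milder.

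This should be fixed. It affects one comparison within one of three aims, and the remedy is wording plus a pre-set criterion.

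**What to change.** 1. Delete the goal of upholding the null hypothesis from Specific Aim 3.
2. Declare comparability only if the 90% CI for the group difference in change lies inside a margin that the sponsor justifies for each key outcome and fixes before data are seen.
3. Replace the Aim 3 power statement with equivalence power at that margin. The Step 4 table shows what to expect at 33 and 25 per group.
4. Reconcile the Study Plan's 75 per cell with the 33 per cell in Statistical Considerations, and base the restated power on the agreed figure.
5. Attribute any narrowing of the racial gap to omentectomy only if the planned race-by-omentectomy interaction, or the randomised omentectomy contrast among African American and Hispanic patients, supports it.
6. If no margin can be justified, report the difference with its CI as descriptive and make no claim of comparability.

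The cost is a protocol wording change, the work of justifying margins, and a less favourable power figure. These changes need no new patients or data.
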